### Subgroup analyses

Failure to consistently implement evidence into improved prescribing decisions has been associated with older physicians and those without specialty certification [56]. While we would like to test the impact of certification, no data exists describing this status that can be linked to our datasets.

Evidence-practice gaps also have been associated with physician reimbursement arrangements, patient volumes, physician gender, site and extent of training, group size, and work load [57]. Thus, we plan subgroup analyses of male versus female physicians, location of practice (urban or rural), practice volume, solo versus group practice, and years since graduation. As before, multilevel, logistic regression models will be used to assess the association between place-of-practice characteristics and target behaviours.

A further analysis of the immediate and delayed impacts of the printed educational material will be performed using time-series analysis and interventional, autoregressive, integrated moving average (ARIMA) modeling [58]. The group to which the patient's practitioner was randomized will be included as a covariate. An immediate change will be defined as a significant shift in prescribing patterns from projected estimates within four months of the intervention. Delayed effects will be measured with simple time-series analysis, such as exponential smoothing and ARIMA models by comparing actual with predicted utilization estimates. Stationarity will be assessed using the autocorrelation function and the augmented Dickey-Fuller test [59]. The auto-correlation, partial autocorrelation, and inverse autocorrelation functions will be assessed for model parameter appropriateness and seasonality. The presence of white noise will be assessed by examining the autocorrelations at various lags using the Ljung-Box test [60].

The question of whether there are differences in response to PEMs for different diseases patient health status levels and health care problems is addressed in the replicates. Differences between these replicates will be discussed, and will not *a priori *be subjected to meta-analysis. In the event of substantial homogeneity of outcomes, we will consider meta-analysis across the replicates.

There will be one analysis for each replicate upon receipt of one year of follow-up data.

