**Methods/design:**

The design is a large, simple, factorial, unblinded cluster-randomized controlled trial. PEMs will be distributed with ***informed***, a quarterly evidence-based synopsis of current clinical information produced by the Institute for Clinical Evaluative Sciences, Toronto, Canada, and will be sent to all eligible general and family practitioners in Ontario. There will be three replicates of the trial, with three different educational messages, each aimed at narrowing a specific evidence-practice gap as follows: 1) angiotensin-converting enzyme inhibitors, hypertension treatment, and cholesterol lowering agents for diabetes; 2) retinal screening for diabetes; and 3) diuretics for hypertension.

For each of the three replicates there will be three intervention groups. The first group will receive ***informed ***with an attached postcard-sized, short, directive "outsert." The second intervention group will receive ***informed ***with a two-page explanatory "insert" on the same topic. The third intervention group will receive ***informed***, with both the above-mentioned outsert and insert. The control group will receive ***informed ***only, without either an outsert or insert.

Routinely collected physician billing, prescription, and hospital data found in Ontario's administrative databases will be used to monitor pre-defined prescribing changes relevant and specific to each replicate, following delivery of the educational messages. Multi-level modeling will be used to study patterns in physician-prescribing quality over four quarters, before and after each of the three interventions. Subgroup analyses will be performed to assess the association between the characteristics of the physician's place of practice and target behaviours.

A further analysis of the immediate and delayed impacts of the PEMs will be performed using time-series analysis and interventional, auto-regressive, integrated moving average modeling.

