### Proposed sample size

We wished to have adequate power to detect modest changes in the way physicians practice. Based on the median absolute effectiveness of PEMs estimated from the Grimshaw review (8%) [7], it would be important to detect 5% and 10% absolute improvements in our target behaviours. Even 5% improvements in the prevalence of evidence-based care for these common conditions will be an important achievement, with significant health benefits for many Ontarians.

In pilot data, the baseline-prescribing rate of ACE inhibitors in persons with diabetes was 36%, and the intra-class correlation for ACE inhibitor use by patients clustered within physicians was 9.2%. With an assumption that one-half of doctors work in solo practices, we ran these data testing power at a mean of three patients and ten patients per practice. Monte Carlo simulations demonstrated that a trial with 1250 practices per arm, with 10 patients per practice and an alpha of 0.05 will provide more than 98% power to detect a 10% absolute increase in the rate of ACE inhibitor use, more than 97% power to detect a 5% absolute increase, and more than 98% power to distinguish between the effects of the combined intervention and either alone, assuming the combined effect to be additive.

Because the baseline rates of the other interventions are comparable or lower (screening for retinopathy, diuretic use, aggressive blood pressure-reducing, and cholesterol-lowering therapies), and the number of patients per practitioner with these conditions is the same or higher, we will have adequate power to detect similar absolute increases for those endpoints.

Later, with the addition (see Table 1) of two groups in the second (patient reminder note) and third (theory-based outsert) replicates, a less comprehensive, but approximate simulation suggested that the impact on power would be minor and would most certainly be greater than the often used target of 80%. The research opportunity that this modification presented was judged to outweigh the likely loss of power. Therefore, we maintained 1,250 practices in the two groups that did not receive an outsert with ***informed***, and assigned 625 practices to each of the four groups who were sent an outsert.

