### Analyses

We hypothesize that the active intervention arms will be superior to control, similarly effective to each other, and with some additive effect when both are delivered. Analyses will be concentrated on this hypothesis.

The study employs a cluster randomized design. The analysis will be carried out using multi-level, hierarchical, logistic regression models, with the trial arm being a physician-level variable, and the prescribing (or screening) outcome a patient-level variable. These models account for clustering of patients within practices, and the consequent lack of independence of prescribing outcomes within a given physician's place of practice [55]. No place-of-practice characteristics, aside from the arm of the trial and baseline adherence to guidelines, will be entered into the model in the primary analysis. With so many physicians randomized to each arm, we anticipate that measured and unmeasured physician factors that might affect the outcome will be equally distributed between the arms. Moreover, including more place-of-practice characteristics in the model would reduce the statistical power to detect the primary outcome.

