## Discussion

We understand very little about the reasons for the gaps between what family practitioners do in clinical practice, and what the evidence-based ideal says they should do. The simplest intervention to narrow these gaps is the PEM, ranging from a one-sentence directive to a long guideline; and they have often been used, but in an intuitive fashion, with neither an underlying theory of behaviour change nor a deep understanding of physicians' barriers to change.

After a 1997 systematic review found their effects to be uncertain, PEMs fell into disfavour. However, a more recent and larger overview found a median improvement of 8% in comparison with no PEM – a result which was similar in effect to more expensive and intensive strategies. Nevertheless, this review cannot overcome the limitations of the primary evidence: the small number of trials (each one of which is small in size), and their continued methodological weaknesses (insufficient power to detect modest effects, and unit of analysis errors). More evidence is needed in order to decide whether PEMs can be used to help change clinical practice.

We have proposed a trial that is designed to address these shortcomings. The large size of the trial provides enough power to confidently and precisely delineate modest effects. Modest effects are important, given the large absolute impact that is achievable when the intervention is applied to a common health problem. By randomizing at the level of the physician place-of-practice, the trial avoids contamination and unit of analysis error. In addition to answering the question of whether PEMs change primary care practitioners' therapeutic decisions, this study, along with its two ancillary studies, also will compare the impact of two types of PEMs (the short, directive versus a two-page descriptive message), and will examine the contextual and sociological factors (e.g., health problems, location, style of physician practice and duration of practice) which may influence the impact of PEMs.

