If passive dissemination of PEMs is shown to be effective, this study may give professional, administrative, and patient organizations interested in change toward evidence-based practice the impetus to develop systematic programs for practice change using PEMs. If shown to be ineffective, use of PEMs as a single practice change intervention would be discouraged, thereby eliminating waste and turning research attention toward other interventions, including a possible role for PEMs as one element in a multi-faceted intervention. If effectiveness is shown to vary by disease problem, barrier, subgroup of practitioner, or any other factor, this study will help inform how different kinds of PEMs should be used in different situations and health problems.

While no economic analysis has been proposed, pending a determination of the effectiveness of PEMs in changing practice, we will collect all costs attributable solely to PEM development, design and dissemination. If the intervention is effective, we will work to set up an initial cost analysis, in which the health care utilization and prescribing changes, if any, of the intervention will be assessed in view of the marginal costs of the PEM intervention. We also will approach professional bodies and patient advocacy groups to offer help in developing PEM strategies for health care quality improvement.

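### As worded, the subgroup models estimate which practices adhere better, not whether practice characteristics change the effect of the printed message

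*Protocol article*

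**What the plan says.** The Subgroup analyses section lists five factors: "we plan subgroup analyses of male versus female physicians, location of practice (urban or rural), practice volume, solo versus group practice, and years since graduation". It gives a reason for choosing them: "Evidence-practice gaps also have been associated with physician reimbursement arrangements, patient volumes, physician gender", followed by further factors of the same kind. It then states the analysis: "multilevel, logistic regression models will be used to assess the association between place-of-practice characteristics and target behaviours". The abstract (Methods/design) gives the same target: "Subgroup analyses will be performed to assess the association between the characteristics of the physician's place of practice and target behaviours".

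The sentence in the Subgroup analyses section refers back to the primary model. According to the Analyses section, that model contains no practice characteristics "aside from the arm of the trial and baseline adherence to guidelines". No interaction between trial arm and a characteristic is mentioned anywhere in the article.

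The Discussion describes what the trial is meant to deliver. It says the study will examine contextual factors "which may influence the impact of PEMs", and gives location, style of practice and duration of practice among its examples. It also describes how the results would be used: "If effectiveness is shown to vary by disease problem, barrier, subgroup of practitioner, or any other factor", they would inform which kinds of message to use in which situations.

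**The concern.** The stated analysis and the stated question concern different quantities. An association between, say, years since graduation and prescribing says who adheres better. It could be estimated without any trial. Whether the message works better in one group than in another is a difference between two randomised comparisons, and needs an arm-by-characteristic term or separate message effects by subgroup.

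An analysis plan that followed the article's wording would contain no test behind the conclusions about subgroups of practitioner that the Discussion anticipates. A characteristic associated with adherence could be mistaken for one that modifies the effect, and a real modifier with no overall association could be missed.

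A smaller point concerns level. The section on allocation defines a practice as all primary care physicians sharing an address. Sex and years since graduation can therefore differ within a practice and are physician characteristics, although the article groups them with place-of-practice characteristics.

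**Working it through.** **1. The plan's own figure.** The article gives no power for subgroups. Its main-comparison power can be checked from Proposed sample size: 36% baseline, ICC 0.092, 1,250 practices per arm, alpha 0.05 (two-sided assumed), 10 or 3 patients per practice (m).
- Design effect = 1 + (m − 1) × 0.092, which is 1.828 for m = 10 and 1.184 for m = 3.
- Effective patients per arm = 1,250 × m / design effect, which is 6,838 and 3,167.
- Power for 36% v 41% is above 99.9% (m = 10) and 98.3% (m = 3). The stated figure of more than 97% holds.

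**2. Does the association identify effect modification?** Three constructed examples with equal cell sizes, each fitted by logistic regression. The characteristic odds ratio (OR) comes from a model with arm and characteristic only. The interaction OR comes from the model with their product added.

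| Example | Group 0: control / message | Group 1: control / message | Characteristic OR | Interaction OR |
|---|---|---|---|---|
| A | 38.5% / 38.5% | 33.5% / 43.5% | 1.00 | 1.53 |
| B | 31% / 35.7% | 41% / 46.2% | 1.55 | 1.00 |
| C | 33.5% / 33.5% | 38.5% / 48.5% | 1.53 | 1.50 |

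The message rates in B come from a common log-odds shift of 0.21 (OR 1.23). For example, 0.31/0.69 × 1.234 = 0.554, and 0.554/1.554 = 35.7%.

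B and C give nearly the same association. In B the message works about equally in both groups; in C it works in one group only. In A there is no association, yet the message effect is 0 points in one group and 10 in the other. The association carries no usable information on modification in either direction, even with arm in the model.

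**3. Precision of the interaction.** The factorial margins have 2,500 practices per side in every replicate. In replicate 1 this is 2 × 1,250. In replicates 2 and 3, outsert is 4 × 625 against 2 × 1,250, and insert is 1,250 + 2 × 625 on each side.
- Variance of the marginal effect = (0.36 × 0.64 + 0.41 × 0.59) / effective n = 0.4723 / effective n.
- m = 10: effective n = 25,000 / 1.828 = 13,676; SE = 0.0059.
- m = 3: effective n = 7,500 / 1.184 = 6,334; SE = 0.0086.
- For a subgroup with share s, interaction SE = SE / √(s(1 − s)).
- Difference detectable with 80% power = 2.8 × interaction SE (2.8 = 1.96 + 0.84).

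| Split (assumed) | m = 10 | m = 3 |
|---|---|---|
| 50/50 | 3.3 points | 4.8 points |
| 20/80 | 4.1 points | 6.0 points |
| 10/90 | 5.5 points | 8.1 points |

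Replicate 3 expects 30,000 patients. Over 5,000 practices that is about 6 each if every patient is counted once, between the two columns.

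With one active arm against control only (1,250 practices each, m = 10, mean effect 5 points), power for a 5-point difference in effect is 85% (50/50), 67% (20/80) and 44% (10/90). For a 2.5-point difference it is 32%, 22% and 14%.

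**The case against.** The strongest reply is that an interaction was meant. In a trial, a subgroup analysis of male versus female physicians ordinarily means the intervention effect in each group, and the reference back to the primary model implies that trial arm stays in. The article also condenses a fuller protocol, and the exact terms of secondary models are commonly left to the analysis plan.

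The intention is plausible, but the text does not supply it. The same association target appears twice, and the factors are justified by their link with the evidence-practice gap, which is a prognostic reason. Where the article does speak of differing response to the messages, it does so for diseases, health status and health problems, and assigns that question to the replicates. Keeping arm in the model does not help without the product term, as the three examples show. The fault is therefore a stated target that does not match a stated question, rather than omitted detail.

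Three stronger readings are tempting and are not supported:
- A reader might infer that the trial cannot answer the subgroup question. Only the models as worded cannot; the data and design can.
- A reader might infer that effect modification is posed for all five factors. The Discussion names location, style and duration of practice. Sex and volume are not named, and none of the three numbered aims concerns modification by physician characteristics.
- A reader might infer that the investigators will report a main effect as a differential effect. Nothing in the article says so; this is a risk of the wording.

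The point about level is also minor. The Analyses section already treats arm as a physician-level variable, so the label is loose rather than a demonstrated modelling error.

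**Conclusion.** The point holds for the models as worded. They target the association of practice characteristics with the target behaviour, and this does not identify whether those characteristics modify the effect of the messages, which is what the Discussion promises to report. The primary comparison is unaffected.

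The defect itself is qualitative and does not depend on the precision figures. Those figures show that the right quantity can be estimated, but only coarsely for unequal splits or few patients per practice. They rest on assumed subgroup shares, a 36% v 41% comparison, additive outsert and insert effects, a normal approximation on the absolute scale, and the article's within-physician ICC applied to practices.

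**What to change.** Reword the Subgroup analyses section, and the matching sentence in the abstract, along these lines: for each listed characteristic, its main effect and its interactions with outsert and with insert are added to the primary model; the subgroup result is the interaction estimate with its 95% CI, shown beside the message effects within each subgroup; associations between a characteristic and the behaviour are reported as descriptive only. Enter physician sex and years since graduation at physician level. Label the subgroup results exploratory.

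The cost is wording in the protocol and analysis plan. No new data are needed. The one drawback is the limited precision of the interactions, which the exploratory label makes plain.

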### Research design

The research design is a factorial, cluster-randomized controlled trial with three replicates [52,53]. ***informed ***is published four times per year. We will conduct three replicates of the trial to cover the three evidence-practice gaps over a nine-month period (three successive mailouts of ***informed***). We will test the effects of short (directive) and long (discursive) PEMs compared with no PEM on the clinical practices of primary care physicians, and on related patient outcomes. Table 1 describes the intervention groups for each of the three replicates. In the first replicate (ACE inhibitors, hypertension treatment, and cholesterol-lowering agents for diabetes), the first intervention group will receive a copy of ***informed ***with both the short, directive, evidence-based outsert stapled to the lower-left quarter of the front page, and the longer two-page insert focusing on the same topic as the outsert. The second intervention group will receive the identical ***informed***, with only the above-mentioned outsert. The third intervention group will receive the identical copy of ***informed ***with the above-mentioned insert. The control group will receive the identical ***informed ***only, without the insert or the outsert. The health care topic shared by the insert and outsert will not be covered elsewhere in that issue of ***informed***. The outsert for this first replicate is shown in Figure 1 and the insert in Figures 2 and 3.

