The Registered Persons Database (RPDB) identifies all persons in the province who are eligible for OHIP coverage. It will be used to link patient participants to the administrative databases, and to detect death and out-migration of patients over the course of the study. Claims from the ODB Program will be used to measure the prescribing changes that result from the interventions. These data are available only for people 65 years of age and older. Accordingly, the two drug-related replicates are restricted to that age group of the Ontario population. The ODB data are delivered to ICES within two weeks of the end of the month of the claim. Claims data from OHIP will be used to identify physician patient linkages, and to measure the delivery of ophthalmologic and optometric screening. All of these datasets are available at ICES, and all bear encrypted health card numbers that are unique to patients but common over time and across data sets.

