### Outcome measurement

Follow-up by means of routine data will cover four quarters before and after each prescribing-related PEM intervention. Each of the process-of-care measures has been used in large-scale studies using databases held at ICES.

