### Recruitment, compliance, loss to follow-up, and drop-out

Practitioners may of course decide to ignore the PEMs or never open the envelope containing ***informed***. We will not know what practitioners will do with the intervention, a normal feature of the pragmatic trial philosophy that tests interventions under real-world conditions. ***informed ***will be mailed in the usual fashion to all identified practitioners. Any practitioners who subsequently remove themselves from the mailing list for ***informed ***will be analysed in the allocated arm on an intention-to-treat basis.

While the unit of analysis is the physician, loss of patients is important to detect in order to maintain accurate denominators for the determination of outcome rates. Patients may be lost due to removal from the system (death or out-migration), or change of provider. The former will be detected in the RPDB, the latter by a plurality rule for prescriptions. For the baseline analysis (pre-intervention period), the initially assigned patients for each physician will be used. For each of the succeeding observation periods (three pre- and four post-intervention), initial patients will be confirmed by eliminating patients no longer eligible according to the RPDB, and ensuring that assigned patients are still being cared for by the study physician through a requirement that the study physician must have written the plurality of the patient's prescriptions in that period.

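### One year of data each side of a mailing cannot support the planned ARIMA and seasonality work, and the immediate and delayed effects are defined against a forecast rather than between randomised arms

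*Protocol article*

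**What the plan says.** On the data span, Outcome measurement states: "Follow-up by means of routine data will cover four quarters before and after each prescribing-related PEM intervention". The section on recruitment, compliance, loss to follow-up and drop-out gives the same count as a baseline period plus three further periods before and four after. The abstract applies the span to all three replicates: "Multi-level modeling will be used to study patterns in physician-prescribing quality over four quarters, before and after each of the three interventions". No longer series is mentioned anywhere.

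On the method, the last part of Subgroup analyses adds a time-series analysis with interventional ARIMA models and exponential smoothing. Stationarity is to be checked by the autocorrelation function and the augmented Dickey-Fuller test, seasonality by three correlation functions, and residual white noise by the Ljung-Box test. The randomised group is to be a covariate. The immediate effect is defined thus: "An immediate change will be defined as a significant shift in prescribing patterns from projected estimates within four months of the intervention". The delayed effect comes from comparing observed with predicted utilisation.

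On timing, Research design says that the periodical "is published four times per year" and that "We will conduct three replicates of the trial to cover the three evidence-practice gaps over a nine-month period", using successive issues. Practices are re-randomised for each replicate (Allocating participants to trial groups).

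The interval of the time series is not stated. The nearest indication is the delivery schedule for drug claims: "The ODB data are delivered to ICES within two weeks of the end of the month of the claim".

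**The concern.** Three things do not fit together.

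- **Series length.** The tests that are meant to justify the projection need far more points than one year each side provides. A seasonality check needs more than one cycle free of the intervention.
- **Estimand.** Both effects are departures from a forecast. The trial has a randomised control arm that would remove season and secular trend, but the definitions do not use it.
- **Window.** Four months is longer than the three-month gap between issues, so the next mailing falls inside the window.

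At stake is how the immediate and delayed results are read. A seasonal swing in prescribing, or a trend already under way, could be reported as a response to the printed message. A message that did work could be hidden by a poorly identified forecast.

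**Working it through.** **1. Reproduce the plan's counts.** Periods: 1 baseline + 3 before + 4 after = 8 quarters, which agrees with four quarters each side. Mailings: 12 months / 4 issues = 3 months apart, and 3 × 3 = 9 months, which agrees with Research design.

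**2. Length of the series.** Quarterly: 4 points before, 8 in all. Monthly: 12 before, 24 in all.

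**3. Can the named checks be run?** A Dickey-Fuller regression with a constant and one lag has 3 coefficients and uses n − 2 points. With n = 4 this leaves 2 points for 3 coefficients, so it cannot be computed. The approximate 95% band for an autocorrelation is ±1.96/√n.

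The table also shows simulated rejection rates at the 5% level (2,000 series per length). The settings are assumptions, not taken from the document: a stationary AR(1) series with coefficient 0.5 and a random walk. Ljung-Box was applied to the AR(1) series itself at up to 4 lags.

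| Points | Meaning | ACF band | Dickey-Fuller rejects: stationary / random walk | Ljung-Box power |
|---|---|---|---|---|
| 4 | quarterly, before | ±0.98 | not computable | 4% |
| 8 | quarterly, all | ±0.69 | 17% / 12% | 4% |
| 12 | monthly, before | ±0.57 | 18% / 10% | 12% |
| 24 | monthly, all | ±0.40 | 37% / 7% | 36% |
| 48 | for comparison | ±0.28 | 85% / 5% | 72% |

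At 8 or 12 points the Dickey-Fuller test hardly tells a stationary series from a random walk. At 24 points it still misses about 63% of stationary series (100 − 37).

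**4. Seasonality.** At either interval there is one annual cycle before the mailing (4/4 or 12/12). Using the whole series does not solve this. Suppose the mean at time t is a fixed seasonal term for that calendar month, plus a linear trend β per month, plus a lasting step δ after the mailing. Each calendar month is seen once before and once after, and its difference is

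after − before = δ + 12β,

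the same for all 12 months. Only the sum is estimable: 14 coefficients (12 + 1 + 1), rank 13. The quarterly version gives δ + 4β: 6 coefficients, rank 5. With separate immediate and delayed steps, only their difference is estimable. Adding arm as a level covariate leaves the deficiency at one. Replacing the common step by an arm-by-period term removes it, because a season and trend shared by the arms cancel in the active-minus-control difference.

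**5. The window.** Put replicate 1 at month 0, replicate 2 at month 3 and replicate 3 at month 6.

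- Replicate 1: the window is months 0 to 4 and the next mailing is at month 3.
- Replicate 2: the window is months 3 to 7 and the next mailing is at month 6.
- In both, 4 − 3 = 1 month of the four follows the next trial mailing. Replicate 3's window meets only an issue after the last trial mailout.
- The longer spans overlap too. Replicate 3's pre-mailing year (months −6 to 6) contains the replicate 1 and 2 mailings, so its projection is not from a mailing-free baseline. Replicate 1's follow-up year contains the diuretic mailing at month 6, and one of its outcomes (Table 2) is receipt of two or more antihypertensives.

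**The case against.** The strongest reply is that the article never says that the ARIMA series is quarterly. The abstract ties the four quarters to the multilevel model and lists the time-series work separately. Drug claims arrive monthly, and a four-month window itself suggests a monthly series. A simple non-seasonal ARIMA can be fitted to 24 points. This stands: a reader might infer that the model cannot be fitted at all, but that follows only for quarterly data. The interval may also be fixed in an analysis plan that is not shown. The span, however, is stated, and one pre-mailing cycle follows from it at any interval.

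A reader might also call the comparison an uncontrolled before-and-after contrast. That goes too far, because the randomised group is a stated covariate. What remains is that both effects are worded as departures from a forecast, and a group covariate without a time or period interaction shifts only the level.

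A third inference would be that the next mailing seriously contaminates the four-month window. The document points the other way. Practices are re-randomised at each mailing, so the next message is balanced across arms in expectation, and its topic differs: eye screening follows replicate 1 and diuretics follow replicate 2. The definition also speaks of prescribing, while replicate 2 measures screening. Re-randomisation protects an arm contrast, not a shift within a series, but the likely bias is small.

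Finally, the plan does not commit to seasonal differencing, and an intervention model normally uses the whole series. Step 4 of the working therefore does not rely on differencing or on the pre-mailing points alone.

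**Conclusion.** The point holds in limited form. On the stated span the time-series plan cannot do what it says. A quarterly series is too short for the named steps. A monthly series allows a simple fit with weak diagnostics, and at either interval seasonality cannot be estimated from pre-mailing data or separated from trend and a lasting effect. Defining both effects against a forecast, with no arm-by-time contrast stated, leaves season and secular trend open to being read as effects of the message. The window exceeds the mailing gap by one month, which is a minor fault.

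This assumes that the one-year span also bounds the ARIMA series, since no other is given. The rejection rates depend on the simulation settings. The rank argument assumes additive fixed seasonality, a linear trend and a lasting step.

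This is a further analysis. The primary multilevel logistic comparison of arms does not depend on it and is unaffected.

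**What to change.** Define both effects as randomised contrasts in the multilevel model already planned, using arm-by-quarter terms: immediate as the arm contrast in post-mailing quarter 1, which ends when the next issue is due, and delayed as the contrast in quarters 2 to 4. The four-month definition then falls away.

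If ARIMA is kept, state the interval and length of the series. Use monthly data with a pre-mailing period of several annual cycles, model the active-minus-control difference, and limit the immediate window to the three-month mailing gap. If older data cannot be drawn, drop the seasonality and stationarity claims.

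The cost is small: a change of wording, some extra analysis and, for the ARIMA version only, extraction of older claims. Randomisation, mailings and the primary analysis stay as they are.
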